#### Sample size calculations and power

We aimed to recruit 350 participants, approximately 30 from each of 12 senior centers. Assumptions included intention-to-treat analyses, 80 % power, two-tailed alpha = 0.05, 90 % retention at 6 months, unit-standardized continuous outcomes, and a linear mixed model of group differences at 6 months. Based upon published data from a study involving older adults who completed a year-long choir program [25], the largest intra-cluster correlation (ICC) for any outcome equaled 0.015. Accounting for ICC, cluster size, and attrition, the minimum detectable group difference, *d*, equaled 0.37, which compares favorably to effect sizes based upon the results reported by Cohen and colleagues [25]: overall health rating (0.41); depression (0.38); number of weekly activities (0.57 and 0.77).

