To date, three longitudinal intervention studies of choral singing for older adults have been completed. Cohen and colleagues (2006) were the first to initiate a large-scale non-randomized study comparing 12 months of participation in a community choir for older adults to a usual activity comparison group. The choir met weekly for 33 weeks over a one-year period. At 12 months (85 % of those enrolled completed the 12 month assessment), those in the choir group reported higher self-rated health, fewer doctor visits, fewer over-the-counter medications, fewer falls, and less decline in morale and loneliness than the comparison group [25]. However, the groups were self-selected (recruited separately into the singing and comparison group), bias due to attrition was not considered, and the sample consisted predominately of non-Latino White women. Nonetheless, improvement in measures of several domains of health and well-being suggested better outcomes for the choir group, an important finding given the lack of prior studies. More recently, Coulton and colleagues completed a randomized controlled trial of a singing program for older adults in England [26]. Adults age 60 and older recruited from senior centers and nearby communities were randomized to a standardized singing program or a usual activity control group. The 90-min singing group met weekly for 14 weeks. There were significant differences between the intervention and control group after three months; participants in the singing group reported significantly higher scores on a mental health summary index and lower depression and anxiety, compared with the control group. Although the participants were randomized to the intervention and control groups, the sample was, again, primarily White women with high educational backgrounds. The outcomes focused only on mental health; thus the possible effects on other health aspects were not evaluated. The third study was a randomized controlled trial of a theater program for lower-income older adults that included a singing group as an active control condition, in addition to a usual-activity control group [27]. However, the authors did not report differences between the two control groups (e.g., between the usual activity group and the singing group). Within-group analyses indicated that the singing group improved on ratings of personal growth over the 4 weeks (p < .001). No other within-group changes were examined for significance.

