### Cluster randomization

Because of the small number of centers involved, simple random assignment of centers to the immediate and delayed start groups could fail to establish equivalent experimental groups at baseline. Therefore, we used restricted randomization (described below) to help ensure balance of center characteristics across experimental groups [32]. We collected data from senior center reports that described the characteristics of each center, including individual-level variables, center-level variables, and readiness for the intervention (Table 1). These variables were used to aid the selection of two matched groups of centers, with each group containing six centers. An algorithm generated all possible partitions of centers into two groups of six centers (462 possible partitions), estimated the profile of center characteristics for each group, and calculated the sum of squared profile differences across groups within each partition. We examined 23 (top 5 %) candidate partitions with the smallest sum of squared profile differences and selected one partition based upon visual inspection of the group-specific profiles. Because recruitment was conducted within staggered pairs of centers, six pairs of centers were created, and each pair included one center from each group. Finally, one group of six centers was randomized to the immediate start group and the other set to the wait-list control group. When recruitment was completed within a staggered pair of senior centers, the randomization assignment was revealed to the corresponding study staff, senior centers, and participants.

**Table 1 Tab1:** Variables used in the restricted randomization process

Level	Variables
Individual level	% needing translation services
	% living alone
	% functionally impaired
	% with “low” income
	% with medical insurance
	% on social security income
	% with nutrition risk
	% age < 60
	% age 60-74
	% age 75-84
	% age 85+
	% African American
	% Asian/Pacific Islander
	% Latino
	% White
	% male
Center level	Whether the following types of activities are offered:
	• cognitive
	• emotional
	• singing
	• arts/crafts
	• health promotion
	• meal service
	• social services
	• transportation services
	• parties/cultural events
	• day trips
Readiness for intervention	Moderately, quite, or extremely

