##### Psychosocial engagement: emotional well-being

We used several measures of emotional well-being, one of which was a primary outcome. The 8-item Patient Health Questionnaire (PHQ-8) [48] was used to assess depressive symptoms as the primary psychosocial outcome. In a previous study with a choir intervention for older adults, Cohen and colleagues found a trend for improvement in depressive symptoms [25]. The PHQ-8 asks participants to rate the frequency of depressive symptoms in the last two weeks including feeling depressed, having little interest in things, having trouble sleeping, being tired, having poor appetite, feeling bad about oneself, having trouble concentrating, and moving slowly. The PHQ-8 has good validity and reliability in diverse community samples [49, 50].

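### The stated detectable difference of 0.37 does not allow for only 12 randomized centers; on the plan's own inputs it is about 0.41, so the favorable comparison with the depression benchmark fails at 80% power

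*Protocol article*

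**What the plan says.** The section on sample size and power in the protocol article sets the target: "We aimed to recruit 350 participants, approximately 30 from each of 12 senior centers". It lists its assumptions as "Assumptions included intention-to-treat analyses, 80 % power", then "two-tailed alpha = 0.05, 90 % retention at 6 months", then "unit-standardized continuous outcomes, and a linear mixed model of group differences at 6 months". It takes an ICC of 0.015, the largest seen for any outcome in an earlier year-long choir study. After allowing for ICC, cluster size and attrition, it reports that the minimum detectable difference "equaled 0.37, which compares favorably to effect sizes based upon the results" of that study: overall health 0.41, depression 0.38, and weekly activities 0.57 and 0.77.

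The section on cluster randomization gives the allocation: "one group of six centers was randomized to the immediate start group and the other set to the wait-list control group". The statistical analysis plan section specifies linear mixed models with random intercepts for centers and participants, fitted to the baseline and 6-month values. Neither section names a degrees-of-freedom method, and the power paragraph states no baseline correlation.

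**The concern.** When whole centers are randomized, clustering costs power in two ways. The design effect enlarges the variance of the group difference, and the paragraph allows for that. In addition, the between-center variance has to be estimated from 12 centers, so the reference distribution for the group contrast has 12 − 2 = 10 degrees of freedom. Nothing in the paragraph allows for that, and the printed figure looks too small for a calculation that did.

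The size of the gap matters because the article draws a conclusion from it. The printed margin over the depression benchmark is only 0.38 − 0.37 = 0.01. Depression is also the one listed benchmark that matches a primary outcome domain (the PHQ-8). A modest correction is enough to reverse that comparison, and a reader of a null PHQ-8 result would be relying on a power statement that is too favorable.

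**Working it through.** **Inputs, all from the sample size section except the allocation (cluster randomization section)**
- Recruited 350; retained 350 × 0.90 = 315
- Centers: 12, six per arm; retained per center m = 315 / 12 = 26.25
- ICC 0.015; SD 1; two-sided alpha 0.05; power 80%

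**Step 1. Standard error of the group difference**
- Design effect = 1 + (m − 1) × ICC = 1 + 25.25 × 0.015 = 1.379
- SE = √(4 × 1.379 / 315) = 0.1323

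**Step 2. Reproduce the printed figure**
- Normal quantiles: (1.960 + 0.842) × 0.1323 = 2.8016 × 0.1323 = 0.371, which is the printed 0.37.
- A t distribution on the individual-level N − 2 degrees of freedom gives 0.372, the same to two decimals.
- Leaving out attrition gives 0.357 and leaving out clustering gives 0.316. So both were included, as the article says.

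**Step 3. Same standard error, 10 degrees of freedom**
- The critical value rises from 1.96 to 2.23.
- Solving the noncentral t for 80% power gives 0.4115, about 0.41.

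| True difference | Power on 10 df |
|---|---|
| 0.37 (printed figure) | 71.3% |
| 0.38 (depression) | 73.5% |
| 0.41 (overall health) | 79.7% |

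**Step 4. Sensitivity to how the inputs are read**

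| Reading | Normal quantiles | 10 df |
|---|---|---|
| 315 retained, m = 26.25 | 0.371 | 0.411 |
| 315 retained, m = 30 | 0.378 | 0.420 |
| 324 retained (360 recruited), m = 27 | 0.367 | 0.407 |
| 324 retained, m = 30 | 0.373 | 0.414 |

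No reading gives 0.37 on 10 degrees of freedom. If the six recruitment pairs were analyzed as matched pairs (5 degrees of freedom), the figure would be about 0.465, so 10 is the more favorable choice.

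**Step 5. Check by simulation** (six against six centers, 26 or 27 retained per center, ICC 0.015, 6-month values only)
- A cluster-level t test, or a mixed-model test with Satterthwaite-type degrees of freedom, has 71–72% power at 0.37 and 73–74% at 0.38.
- A mixed-model test referred to the normal distribution has about 78–79% power at 0.37, but its type I error is about 5.9%. So 80% power and a 5% alpha are not both met at 0.37 under that test either.

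**Step 6. Comparison with the benchmarks at 80% power**
- Depression: 0.38 < 0.41, not met
- Overall health: 0.41 against 0.41, a tie
- Weekly activities: 0.57 and 0.77 > 0.41, met

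**The case against.** **Baseline data.** This is the strongest objection. The planned model uses baseline and 6-month values jointly, whereas the calculation above uses only the 6-month contrast. With baseline adjustment on 10 degrees of freedom (SE multiplied by √(1 − r²)), the figure would be about 0.39 at r = 0.3, 0.36 at r = 0.5 and 0.33 at r = 0.6. It drops below 0.37 once r exceeds about 0.44. These correlations are assumed, since the article gives none. With normal quantiles, the group-by-time term in the planned model, which has no center-by-time effect, would fall below 0.37 for r above about 0.31. This part stands: a reader might infer that the trial as analyzed is underpowered, and the document does not show that. It does not rescue the printed figure, which is claimed for the group difference at 6 months with no baseline gain stated.

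**The ICC is an upper value.** The 0.015 is the largest ICC for any outcome, so the ICC for depression in that study is no higher. At an assumed 0.007 the 10-df figure is 0.380, and at 0.005 it is 0.372. But depression's own ICC is not given, and the article computed 0.37 at 0.015. In the other direction, ICCs above 0.015 have no source in the document, so a larger shortfall cannot be claimed.

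**The critical values are inferred.** The article does not say which were used, and the full protocol or SAP may name a degrees-of-freedom method. That is so. The inference is that normal or individual-level values reproduce 0.37 and 10 degrees of freedom does not. The point concerns a number that is printed and a conclusion drawn from it, not a missing method.

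**Benchmark quality.** The Background says of the earlier study that "the groups were self-selected (recruited separately into the singing and comparison group), bias due to attrition was not considered", and the primary outcome section says that it "found a trend for improvement in depressive symptoms". A reader might infer that the 0.38 is too optimistic. The article states no direction of bias, so that does not follow; the passages support only caution in leaning on the figure.

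**Conclusion.** Wrong as written. On the article's own inputs, the detectable difference at 80% power and two-sided 0.05 is about 0.41 (0.407 to 0.420 across readings of the cluster size), not 0.37. The favorable comparison does not hold at 80% power for depression and only ties for overall health.

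This rests on centers as the unit of inference with 10 degrees of freedom, an ICC of 0.015, and a 6-month contrast that gains nothing from baseline.

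A reader might go further and conclude that the trial cannot detect a depression effect of 0.38. That is not supported: power there is about 74%, some 6 points short of nominal.

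**What to change.** In the sample size paragraph, restate the minimum detectable difference as about 0.41 (80% power, two-sided 0.05, 10 degrees of freedom) and report 71% power at 0.37. Confine the favorable comparison to weekly activities, note the tie for overall health, and say that power at the depression benchmark is about 74%.

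Alternatively, if the sponsor relies on baseline information in the planned mixed model, state the assumed baseline correlation with its source and quote the 10-df figure that follows from it, for example about 0.36 at an assumed r = 0.5.

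A table of detectable differences over a range of ICCs would be useful but is optional. The cost is one reworded paragraph with a less favorable number (or one added assumption). Design and recruitment stay as they are; the article dates enrollment as ending in August 2015, so the sample size was already settled.

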## Discussion

Our study and the choir intervention are unique in several ways. First, we involved several community-based organizations in the design of both the study and intervention. Early in the process, we discussed and received feedback from the community about the research questions, study design, and community choir program by both experts in delivering services to older adults and music professionals. By following this principle of community-based participatory research, the choir program was designed to be inherently responsive to the needs of older adults and to reflect the cultural and other values of the participating community organizations.

By conducting this study in existing AoA-supported senior centers, at its conclusion, the intervention will already be embedded in these settings; thus it will be one step closer to large-scale implementation. The project also supports the value of interdisciplinary collaborations between different types of community-based organizations (e.g., senior centers and community music programs). Such collaborations can help build new relationships between sectors that do not traditionally work together. By engaging a community music center, it may be in a position to continue to offer the choir program under its auspices. Community music centers often have a cadre of trained choir directors and accompanists, and can thus provide some of the needed infrastructure.

Our study is one of the first to design and test the effect of an arts-based intervention for older adults study that specifically focuses on improving multiple, key domains of health and well-being relevant to older adults (i.e., cognitive health, physical functioning, emotional well-being, and social connectedness). We systematically designed the intervention to specifically involve components that would directly impact these multi-dimensional set of outcomes. Thus, the Community of Voices program involves three important areas of engagement (i.e., cognitive, physical and psychosocial). This is much more engaging than a typical sing-along approach to group singing for older adults.

Another important aspect of the study is that we aimed to recruit a large number of ethnically diverse older adults to address health disparities among older adults. Because diverse older adults are projected to account for a large proportion of older adults in the next several decades [3], it is important to develop health promotion programs that can not only reach them but also be easily adapted for a variety of cultures and languages. Community choirs are well-suited for addressing disparities because they can be maximally tailored to accommodate cultural backgrounds. Further, any one choir can be multi-cultural in composition; thus the music can potentially be used to increase awareness of different cultural traditions and cross racial/ethnic barriers. If successful, this trial will add to possible interventions that can help eliminate or reduce some health disparities among older adults.

The Community of Voices program has potential for widespread scalability because it is practical and relatively low-cost to deliver and administer. The nature of the choir is such that it can be folded into an existing activities schedule at senior centers with virtually no additional infrastructure. All that is required is a room to hold sessions (e.g., an activities room or auditorium) and a professional choir director/accompanist who can deliver high quality choral music. The choir can be an additional activity or lifelong learning opportunity that can be offered by many types of community-based organizations serving older adults (e.g., senior centers, community music centers, assisted living facilities) to help older adults remain healthy, independent and engaged, in addition to more traditional health-promotion activities such as exercise and nutrition programs. Thus, choral singing may have the potential to be easily translated into a number of community settings and reach a large number of diverse older adults.

Our study design reflects some methodological considerations. First, we decided to use an intervention and wait-list control condition; we were not able to add a third “active control” arm to the study due to cost limitations. We were also not able to blind the persons conducting the assessments, as the location of the assessment in specific senior centers signaled the arm of the study, and the costs to employ both study coordinators and testers were prohibitive. We decided to perform the assessments in the senior centers to maximize the convenience for the study participants, particularly for those from diverse backgrounds where traveling to a large academic research center might be a barrier. One way to get around this barrier would be to set up temporary assessment sites (not associated with the senior center) in the community and arrange for transportation, but this would also take additional resources. To reduce risk of bias, all study personnel were not made aware of the randomization assignment before it was revealed, and we will not examine any longitudinal data before all sites complete their 6-month randomized arm of the study.

In conclusion, the study is an example of a novel translational approach to address health disparities in which multiple inputs were integrated to create an intervention (evidence-based research, best practices, and the perspective of the communities in which the intervention is to be offered). This translational approach also enabled a rigorous scientific design (randomized controlled trial) to be applied to an intervention delivered in existing community settings. If the Community of Voices program is successful, it will provide an example of how encouraging participation in the creative arts (including singing) could be a new strategy for promoting health and well-being of older adults through community-based programs.

## Abbreviations

AoA: Administration on Aging
CAT: Computer adapted testing
CEA: Cost effectiveness analysis
DAAS: Department of Aging and Adult Services
EQ-5D: EuroQol five dimensions questionnaire
ICER: Incremental cost-effectiveness ratio
ICC: Intra-cluster correlation
IRT: Item response theory
NIH: National Institutes of Health
PHQ-8: 8-item patient health questionnaire
PI: Principal investigator
SES: Socioeconomic status
SPPB: Short Physical Performance Battery
QALYs: Quality adjusted life years
TMT: Trail making test
US: United States
